## Abstract

**Background:**

Internet-based cognitive-behavioral therapy (iCBT) is more effective when it is guided by human support than when it is unguided. This may be attributable to higher adherence rates that result from a positive effect of the accompanying support on motivation and on engagement with the intervention. This protocol presents the design of a pilot randomized controlled trial that aims to start bridging the gap between guided and unguided interventions. It will test an intervention that includes automated support delivered by an embodied conversational agent (ECA) in the form of a virtual coach.

**Methods/design:**

The study will employ a pilot two-armed randomized controlled trial design. The primary outcomes of the trial will be (1) the effectiveness of iCBT, as supported by a virtual coach, in terms of improved intervention adherence in comparison with unguided iCBT, and (2) the feasibility of a future, larger-scale trial in terms of recruitment, acceptability, and sample size calculation. Secondary aims will be to assess the virtual coach’s effect on motivation, users’ perceptions of the virtual coach, and general feasibility of the intervention as supported by a virtual coach. We will recruit *N* = 70 participants from the general population who wish to learn how they can improve their mood by using Moodbuster Lite, a 4-week cognitive-behavioral therapy course. Candidates with symptoms of moderate to severe depression will be excluded from study participation. Included participants will be randomized in a 1:1 ratio to either (1) Moodbuster Lite with automated support delivered by a virtual coach or (2) Moodbuster Lite without automated support. Assessments will be taken at baseline and post-study 4 weeks later.

**Discussion:**

The study will assess the preliminary effectiveness of a virtual coach in improving adherence and will determine the feasibility of a larger-scale RCT. It could represent a significant step in bridging the gap between guided and unguided iCBT interventions.

**Trial registration:**

Netherlands Trial Register (NTR) NL8110. Registered on 23 October 2019.

## Background

The most widely studied online interventions for depression are those based on cognitive-behavioral therapy (CBT) [1]. Such interventions may be guided or unguided. Guided interventions typically include regular feedback and support by professional health care workers, licensed therapists, or trained volunteers, either via secured email exchange or via messaging systems within the intervention platforms. In shorter interventions, mostly up to eight sessions, support often takes the form of coaching, but in more intensive types of treatment, it may be more therapeutic in nature. Guided interventions have been found more effective in terms of symptom improvement [2–5]. That may be explained by a more positive effect of the guidance on motivation and engagement, and hence on adherence rates [6, 7]. However, as guided interventions require the involvement of supportive humans, unguided interventions are potentially more scalable, more accessible, and less expensive [8]. This study is part of a project to bridge the gap between guided and unguided self-help internet-based CBT (iCBT) interventions for depression, using *embodied conversational agents* (ECAs) to automate coaching support. ECAs are more or less autonomous and intelligent software entities with a graphical embodiment. They are used to communicate with the user [9].

The idea of using ECAs in psychological treatment procedures goes back roughly a decade [10], and a recent scoping review has shown that many different such applications have since been developed for a variety of common mental health disorders [11]. In the context of depression, ECAs have been proposed for a broad range of applications. For example, ECAs have taken on the role of an interviewer that engages in face-to-face interaction with users to make them feel more comfortable in talking about and sharing distressing information [12], or the role of a virtual nurse who guides hospital patients with depression through their discharge procedure [13], or that of an empathic therapist who helps people navigate the Beck Depression Inventory questionnaire [14]. A number of studies have applied ECAs in the context of an iCBT for depression. Study designs varied widely. Martínez-Miranda and colleagues conducted a pilot study in which an ECA supported users throughout a CBT intervention [15]. Their evaluation, involving *N* = 8 adult participants with mild to moderate depression, focused primarily on the feasibility of the cognitive change model employed by the ECA to regulate its own emotional responses, for example by providing more empathic feedback or facial expressions. In a randomized controlled study by Kelders of an online acceptance and commitment therapy involving *N* = 134 adults with mild to moderate depression, half of the participants received automated feedback accompanied by a picture of a clinician and the other half received human support [7]. The study concluded that, although participants receiving human support were more involved in the intervention than those receiving automated feedback (as scored on the Personal Involvement Inventory [16]), they were not significantly more adherent in terms of intervention completion. A pilot study by Ring and colleagues aimed to create a one-on-one therapeutic conversation with a virtual counselor [17]. In a pre–post-test study design including *N* = 10 participants with mild to moderate depression, most users reported that the agent understood their emotions, but no significant improvements in depressive symptoms were found. Another pre–post-test pilot study investigated the acceptability and usability of a user-adapted, ECA-supported interactive platform addressing depression and suicide symptoms in a convenience sample of *N* = 60 participants [18]. It concluded that system usability and the acceptability of the agent’s emotional responses were sufficient for the researchers to continue preparing the system for an initial clinical trial. A study by Fitzpatrick and colleagues looked at the feasibility, acceptability, and preliminary effectiveness of a conversational agent called Woebot, which delivered CBT-based self-help content in a text-based conversational format [19]; *N* = 70 university students who self-identified as experiencing depression and anxiety symptoms were randomized to using Woebot or to reading a book on depression. The intervention group reported significant reductions in depressive symptoms compared with the control group (*d* = 0.44). In another study, Suganuma and colleagues investigated the feasibility and acceptability of an ECA-delivered CBT-based intervention that aimed to determine users’ mental and physical status in order to make appropriate behavioral suggestions. A non-clinical intervention group of *n* = 191 users was compared with *n* = 263 study participants who did not use the intervention. The intervention showed some initial effectiveness in terms of mental health improvement [20]. Many of the applications described in this paragraph were judged acceptable and feasible, and some of the studies even showed that positive treatment effects can be accomplished using ECA-based interventions (e.g., [19, 20]).

Although the studies just reviewed have shown promising results, most did not focus on ECAs in a supportive role as an adjunct to an iCBT intervention (intervention + ECA), but rather on the ECA as a medium through which iCBT could be delivered (intervention = ECA). In order to strengthen the evidence for the use of ECAs as an adjunct to improve iCBT interventions, a study would need to compare an ECA-supported intervention with the same intervention with either human support or no support. Of the studies cited above, only the one by Kelders [7] used such a design. That study, however, focused primarily on automated support through text messages, with the support embodied with a picture of a clinician. Though this does satisfy our criteria for what an ECA is, we might question how well the results generalize to interventions utilizing more sophisticated ECA technology. We aim to address this gap in the literature by comparing outcomes of participants in an existing intervention with added ECA support (our intervention group) with the outcomes of participants in the same intervention without ECA support (our control group). Our general hypothesis is that by simulating a number of human support factors—specific factors such as motivational interviewing techniques and feedback to CBT exercises and common factors such as empathic communication [21]—an ECA can positively affect motivation and engagement, and thereby adherence rates. This, in turn, may increase the clinical effectiveness of iCBT interventions in which traditional human support is unavailable [22]. Given the novelty of our approach, which combines an existing iCBT intervention with ECA support, we have opted for a pilot randomized controlled trial, whose primary aims will be to compare adherence rates between the two study groups and to assess the feasibility of a future larger-scale trial. Secondary aims include assessing within- and between-group participant motivation for performing and continuing the intervention, gauging users’ acceptance of and perceived relationship with the supportive ECA, and estimating the feasibility of the entire system in terms of user satisfaction, usability, and preliminary effectiveness.

## Methods/design

### Study design

The study is designed as a pilot non-blinded two-armed randomized controlled trial (*N* = 70) in which people with low mood from the general population will be randomly allocated either to an intervention for improving mood with automated support delivered by a virtual coach (*n* = 35) or to the same intervention without the automated support (*n* = 35). The study protocol has been approved by the Medical Ethics Committee of the VU University Medical Centre, Amsterdam (registration number 2019.388). Written informed consent will be obtained from all participants. Figure 1 displays the flowchart of the study design in accordance with the SPIRIT guidelines [23, 24].

**Fig. 1 Fig1:**
[figure not shown]
Flowchart of the study design

### Assessments

Assessments will be taken after enrollment (T−1), at baseline (T_0_), and at the end of study participation 4 weeks after baseline (T_1_). Questionnaires will be self-administered and completed online. Table 1 provides an overview of the measures employed at specific time points.

**Table 1 Tab1:** Measures administered at each assessment interval

Questionnaire	Aim	Enrollment (T−1)	Allocation (T_0_)	Post-study (T_1_)
Mental health				
PHQ-9	*Screener*	X		
HADS-D	*Mental health*		X	X
Feasibility				
SUS	*System usability*			X
CSQ-I	*User satisfaction*			X
Study completion	*Reasons for non-adherence*			X
Motivation				
SMFL	*Current use*		X	X
Continued use	*Continued use*			X
Coach acceptance				
WAI-SR*	*Relationship*			X
Acceptance*	*Acceptance*			X

*Applies to the intervention group only

### Participants

#### Inclusion criteria

People from the general population in the Netherlands, aged 18 years or older, will be eligible for recruitment if they express a desire to learn how to improve their mood.

#### Exclusion criteria

Candidates will be excluded from the study if they (i) are not willing to sign the informed consent form, (ii) do not have adequate proficiency in the Dutch language, (iii) do not have a computer with internet access, (iv) do not have a smartphone, (v) do not have a valid email address, (vi) have moderate to severe depression, or (vii) are identified as at risk for suicide. The Patient Health Questionnaire-9 (PHQ-9) will be used to assess whether exclusion criteria *vi* and *vii* apply. Excluded candidates will receive an email detailing the reason for their exclusion. If exclusion criterion *vi* applies (a score of 15 or higher on the PHQ-9), they will be advised to contact their general practitioner, and if *vii* applies (a score of 1 or higher on PHQ-9 item 9), they will also be referred to a national help and crisis line for people at risk of suicide (https://www.113.nl).

### Recruitment

Participants will be recruited in an open recruitment strategy via advertisements in digital media (Facebook, Google Ads) and http://www.link2trials.com. Interested persons will be invited to express their interest in participation by filling out a web form, after which they will receive an information brochure and an informed consent form. People who sign the consent form will receive a link to the online screening questionnaire and, once found eligible for participation, will be sent final instructions and login credentials for taking part in the study. Participants will receive 30 euro if they complete the T_1_ assessments, irrespective of how much time they have committed to the course. They will be free to discontinue study participation at any time, and participation places no restrictions on their use of alternative sources of help.

### Randomization and blinding

Participants will be randomly assigned by an independent researcher to either Moodbuster Lite with automated support (intervention group) or Moodbuster Lite without automated support (control group). That will take place in a 1:1 ratio and on the basis of a computer-generated block randomization table with random block sizes [25]. Group allocation cannot be blinded to participants, because a description of the study’s research aim—improving intervention adherence with automated support by a virtual coach—must be provided in the information letter; whether or not automated feedback is provided will hence be obvious to participants. The principal investigator, who coordinates the study and conducts the data analysis, will not be blinded to the participants’ group allocation.

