### Trial organization

The study is run from VU University Amsterdam, with no other study centers participating. The principal investigator is responsible for coordinating the study, which includes the recruitment of participants and the informed consent procedure, responding to questions and requests from (potential) participants, providing participants with access to the study materials, monitoring participants throughout the study, handling participant reimbursements, data collection, and reporting on the progress of the study to the steering committee members and medical ethical committee. The steering committee (see title page for members) agreed on the final version of this protocol and is responsible for reviewing the progress of the study, and for agreeing on changes to the protocol or study materials, if necessary, to keep the study running properly. Meetings of the steering committee are scheduled when necessary. The trial management committee is composed of the principal investigator and project leader. It is responsible for the study planning, organization of steering committee meetings, reporting to the medical ethical committee of study progress, maintenance of the trial master file, budget administration, and data verification. The trial management committee meets on a monthly basis. An IT team is responsible for the maintenance of the intervention platform and data collection from the platform. As this is a relatively small pilot study, there is no Stakeholder and Public Involvement Group.

Earlier large-scale research using the Moodbuster platform did not result in any known serious adverse events (SAEs) or serious adverse device events (SADEs). If SAEs or SADEs do occur, they will be discussed in the research team and reported to the Dutch Health and Youth Care Inspectorate. Any other adverse events reported spontaneously by the participants or observed by the investigators will be recorded. Due to the low-risk nature of the study, there is no anticipated harm and compensation for trial participation. Participants can contact an independent researcher if they run into issues during the study, and a licensed psychiatrist can be consulted in case issues of a medical or mental health related nature arise.

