### Statistical analysis

#### Primary analysis

The primary analysis will focus on the preliminary effectiveness of the virtual agent with respect to intervention adherence, as assessed in terms of intervention completion and mood recording response rates. Intervention completion will be assessed by calculating point estimates with corresponding 95% confidence intervals for both the intervention and the control group; a general linear model will be used to estimate the preliminary effect at the alpha < 0.05 significance level. That information will enable us to calculate the sample size required for observing a similar intervention effect in a larger RCT. To assess the mood recording response rate, we will conduct a logistic mixed-effects analysis to determine variations in adherence over time, following a similar analysis we performed in a previous ecological momentary assessment study [52].

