#### Data management

On the informed consent form, participants will be asked if they agree to the use of their data in future research on the same topic at VU University, and to their data being shared with regulatory authorities when required. This trial does not involve the collection of biological specimens for storage. All raw data will be stored on a secure local server at the VU University in Amsterdam, which is regularly backed up. Paper-based documents will be stored in a keycard-secured archive at the Department of Clinical, Neuro- and Developmental Psychology. All participants will be de-identified upon randomization by linking their participant number to a random study participant code. In the study, participants will be referred to exclusively by that participant code, and the document linking the two numbers will be destroyed once the study is over and results have been disseminated. Because this study is relatively small and investigator-initiated, no data monitoring committee or auditing process is required. Because we do not expect serious negative outcomes for the participants, we do not conduct an interim analysis and there are no subsequent formal stopping rules.

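### The principal investigator runs the primary adherence analysis unblinded, without a stated reason, although it could be masked and locked if both arms were scored on their common pages

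*Protocol article*

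**What the plan says.** Under Randomization and blinding, the protocol article states: "The principal investigator, who coordinates the study and conducts the data analysis, will not be blinded". That section gives a reason for not blinding participants (the information letter has to describe the virtual coach). It gives none for the analyst. It also says: "Participants will be randomly assigned by an independent researcher".

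Under Trial organization, the principal investigator's tasks include "responding to questions and requests from (potential) participants, providing participants with access to the study materials, monitoring participants throughout the study". Data verification lies with the trial management committee, and "The trial management committee is composed of the principal investigator and project leader". On platform data the section adds: "An IT team is responsible for the maintenance of the intervention platform and data collection from the platform". Data management states that "no data monitoring committee or auditing process is required".

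The primary outcome (Adherence section) is pages completed divided by the maximum number of pages, with a different maximum in each arm. A second adherence measure is the number of mood ratings out of 84. Under Primary analysis, for intervention completion, "a general linear model will be used to estimate the preliminary effect" at the 5% level. A logistic mixed-effects model is named for the mood responses. The completion result is to feed the sample size of a larger trial.

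**The concern.** The person who produces the main estimate knows every allocation and has dealt with the participants. Log-based outcomes remove assessor judgement, but someone must still turn log entries into an adherence score. Where the rule for doing so is not fully fixed, choices made with the arms visible can lean, without intent, towards one result.

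What is at stake is the pilot's main output: an adherence difference that is tested at 5% and carried into the design of a later trial. An estimate that is too large would leave that trial too small.

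**Working it through.** **1. Figures that can be reproduced.** Mood prompts: 3 per day × 7 days × 4 weeks = 84, as stated, and the same in both arms. Sample size: 35 + 35 = 70. The article gives no effect size, SD or power, so there is no power calculation to reproduce.

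**2. Page totals.**

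| Source | Lesson 1 | Lesson 2 | Lesson 3 | Total |
|---|---|---|---|---|
| Adherence section, intervention | 22 | 13 | 20 | 55 |
| Adherence section, control | 20 | 11 | 17 | 48 |
| Table 2 | 22 | 11 | 17 | 50 |

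Table 2 agrees with the intervention count for lesson 1 and with the control count for lessons 2 and 3. Its total matches neither arm.

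**3. Conditional coach pages.** The arms differ by 2, 2 and 3 pages, 7 in all. These equal the maximum numbers of coach conversations in Table 2 (2, 1–2 and 2–3), so each conversation appears to count as one page. The minimum is 2 + 1 + 2 = 5, because the Conversations section makes pre-lesson conversations depend on low motivation or a negative evaluation. An intervention participant who completes everything offered, but triggers no conditional conversation, has 48 + 5 = 53 pages. That scores 53/55 = 0.964 if the untriggered pages stay in the denominator and 53/53 = 1.000 if they do not. The gap is 2/55 = 3.6 percentage points, and it can arise in one arm only.

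**4. Counting window.** The 4-week window is explicit for mood ratings. For pages, participants are advised but not required to finish in 4 weeks, and they keep access for about 5 more months. The article does not tie the page count to a cut-off.

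**5. Would coding the arms A and B mask the analyst?** Not with the outcome as defined. 55 = 5 × 11 and 48 = 2⁴ × 3 have no common factor, so the fractions k/55 and k/48 coincide only at 0 and 1. The exact score of every partial completer therefore identifies the arm. Rounding to whole percentages leaves 28 shared values, out of 56 possible in the intervention arm and 49 in control. Scoring both arms on the same 48 pages removes the leak. The mood denominator of 84 does not leak.

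**6. Illustrations. None of the assumed inputs is in the documents.**

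- Analyst choice. Assume 2, 3 or 4 defensible analyses with test statistics correlated 0.9, 0.8 or 0.7, and that any significant one is reported. The chance that at least one |z| exceeds 1.96 under no effect is 7%, 10% or 13%.
- Consequence for the later trial. By n per arm = 2(1.96 + 0.84)²/d², a true effect of 0.30 SD needs 175 per arm for 80% power. If the pilot suggested 0.40 SD, 99 per arm would be planned, and power at the true 0.30 SD would be 56%.
- Precision of the pilot. The 95% half-width is 1.96 × √(2/35) = 0.47 SD, so sampling error would outweigh a shift of 0.10 SD in any single result. Unlike bias, however, it has no preferred direction.

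**The case against.** The arrangement is openly disclosed, in a small single-centre pilot whose effect is called preliminary. Both adherence measures are recorded by the system. The denominators are stated by arm, and the model types are named. An IT team collects the platform data, participants are coded on randomization, data verification includes the project leader, and the anonymized analysis data will be published so that others can test alternatives. Cut-off dates and scripts commonly belong to an analysis plan that is not shown here.

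Most of this stands, and it limits the severity. It does not supply a reason for an unmasked analyst. Nor does it settle a page score whose totals disagree within the article and whose conditional pages fall in one arm. The missing cut-off carries little weight alone; it is one more choice that would be made with the arms visible.

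Three stronger readings are tempting, and the documents do not support them:

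- **Unequal contact biases the result.** The Background offers the motivating effect of guidance only as a possible explanation for better outcomes. The contact described for the principal investigator is answering questions, giving access and undefined monitoring. No differential contact or prompting to adhere is described, and a condensed article may leave out contact procedures. With an assumed SD of 0.35 (SE = 0.35 × √(2/35) = 0.084), an assumed shift of 3, 5 or 10 points would give false-positive rates of 6%, 9% or 22%. Nothing in the documents points to any such shift, and masking the analysis would not prevent it.
- **One person controls the data from collection to result.** Data collection is among the principal investigator's tasks, but collection from the platform, where page completion is recorded, is assigned to the IT team.
- **Relabelling the arms would be enough.** Step 5 of the working shows that it would not.

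**Conclusion.** The point holds as a moderate and inexpensive improvement. The article states outright that the analyst is unblinded, gives that role participant contact and monitoring, and offers no reason for leaving the analysis unmasked. The remaining discretion lies in the page score: totals of 55 and 48 against 50, up to 2/55 (3.6 points) in one arm from untriggered conversations, and no stated page cut-off. The 3.6 points rest on reading each coach conversation as one page, which the counts support but the article does not say.

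The documents do not allow the bias to be quantified. The 7% to 13% error rates and the 99 against 175 per arm show what could follow under assumed inputs; they are not estimates for this trial. There is no evidence that the result will be biased. The case for acting is that the estimate is meant to size a later trial and that the means of protecting it are already in place.

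**What to change.** 1. **Adherence section:** reconcile the page counts with Table 2, then define completion in both arms on the pages common to both (48 by the Adherence section). Without this, the denominators reveal the arm.
2. **Randomization and blinding:** state that the IT team or the independent researcher supplies a file without participant identifiers, with arms coded A/B, holding only the common-page score and the mood-response counts. The counts should be kept by day or prompt, because the planned mixed model looks at change over time.
3. **Same section:** state that the principal investigator runs a dated, locked script on that file before the codes are opened. The script should include the page cut-off. It also protects the analysis if the arms can be guessed, for instance from unequal group sizes.
4. Measures taken in the intervention group only are analysed after the codes are opened.

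**Cost:** a redefined page score, one coded export and a short delay before unmasking, with no added participants and using roles already in the trial. Masking covers only measures common to both arms and does not address any unequal contact during the study.
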